#### Restricted predictor model

We will include the following three predictors to ensure face-value validity of the prediction model: age, sex and history of previous suicide attempt. We will identify the top 30 predictors that contributed most to predictive performance in each of the base models in stage A (see section Model development). We will pool these predictors and include those deemed important based on clinical input, alongside the three face-value predictors.

### Missing values

We will exclude predictors where more than 20% of values are missing. In remaining predictors, if it is deemed that there is missingness at random, we will consider multiple imputation methods.^26^

### Model validation and goodness of fit

Overall classification performance using area under the receiver operating characteristic curves (AUC) will be estimated for all models; 95% CIs will be calculated using DeLong’s method.^12 27^

For the broad variable search model and for the selected restricted predictor model, we will assess the predictive performance of the trained models using: Concordance Index, Brier Score and a calibration plot.^12 14^

For the broad variable search model and for the selected restricted predictor model, we will also asses sensitivity, specificity, positive and negative predictive values at the risk threshold of 1%, given that this is the approximate prevalence of suicidal behaviour within 30 days after SSRI initiation in Swedish registers.^25^ That is, any child, adolescent or young adult with a predicted risk greater than 1% have a risk that is higher than what is expected in the population, and can therefore be considered ‘high-risk’.^14 28^ We will also report calibration performance at a 2% and 5% risk cut-off.

The impact of different risk score cut-offs could be further evaluated in future work—however, continuous risk scores could provide a more flexible idea of individual risk as compared with risk cut-offs.^28^

We will follow the Transparent Reporting of a multivariable prediction model for Individual Prognosis or Diagnosis (TRIPOD) guidelines.^29^

### Model development

Throughout the paper, we will employ different machine learning models: XGBoost (XG), neural net (NN), EN and support vector machines (SVM).^12 30^

We will develop all models in a sample (‘training sample’) using all data from 1 January 2007 to 31 December 2017. We will apply shrinkage procedures where appropriate, for example, by employing an EN.

We will validate all models in a sample (‘testing sample’) using all data from 1 January 2018 to 31 December 2020. That is, no random sampling will be performed for either training or testing sample.

As a secondary validation, we will validate the final restricted model in the period 1 January 2018 to 28 February 2020 to see if the model performance is influenced by the COVID-19 pandemic.

#### Broad predictor model

For each model XG, NN, EN and SVM, we will identify hyperparameters by a grid search with 10-fold stratified cross-validation, ensuring an approximately equal proportion of individuals with the outcome in each fold. We will use the AUC as the evaluation criterion for hyperparameter tuning^30^—that is, we will choose the set of hyperparameters that maximise the AUC for each model.

After model tuning, we will combine the predictions from all the different models. The class probabilities of each model will be summed and averaged—the final prediction will consist of the class with the highest average probability (ie, we will produce an ensemble prediction). In effect, the predictions of each model will be weighted equally.

Finally, the 30 predictors that are most important (ie, contributed most to the predictive performance) in each of the base models (when applied in the training data) will be extracted using permutation-based feature importance, if computationally feasible. The pooled list of these predictors will then be considered for inclusion in the restricted predictor model based on clinical input and the available evidence base on the risk factors; the original set of pooled predictors will be presented, and we will describe our reasoning for the final predictor inclusion in the paper.

If permutation-based feature importance is not computationally feasible, we will consider the most important predictors based on the predictor importance score from the XG model and absolute beta coefficients from the EN model.

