## Abstract

**Introduction:**

There is concern regarding suicidal behaviour risk during selective serotonin reuptake inhibitor (SSRI) treatment among the young. A clinically useful model for predicting suicidal behaviour risk should have high predictive performance in terms of discrimination and calibration; transparency and ease of implementation are desirable.

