#### Restricted predictor model

For each model XG, NN, EN and SVM, we will identify hyperparameters by a grid search with 10-fold stratified cross-validation, ensuring an approximately equal proportion of individuals with the outcome in each fold. We will use the AUC as the evaluation criterion for hyperparameter tuning.^30^

We will then compare the predictive performance of the different models when including the restricted set of predictors in the testing sample, using the DeLong method to assess statistical significance of the difference. We will also produce an ensemble prediction in the same way as described for the broad predictor model. If there is no model that performs better than the others in terms of AUC score (including the ensemble model) and calibration performance, we will consider the EN model as the final restricted predictor model.^15^ If there is a model with statistically significantly better AUC performance compared with the others (including the ensemble model), this model will be selected as the final restricted predictor model.

We favour the EN model in absence of clear superiority because this multivariate regression approach allows more transparency: the intercept and each predictor coefficient can be reported, allowing a prediction score for each study participant to be easily calculated by clinicians. This intercept of the model, which is a transformation of the baseline risk in the population, can also be changed to fit the particular population considered. In other words, an EN model would allow for greater transparency and scalability, including easy dissemination of the model as an online tool.^14^

Given the parameter selection inherent in an EN model, it is possible that even in the broad predictor model step it produces a model with fewer than 30 predictors. If this model already at the stage of the broad predictor model has a predictive performance superior to or equal to the other models, we will consider bypassing stage B of this protocol and using this model as the final model.

In the final model, we will assess the prediction performance in terms of the AUC in the subset of individuals who received a diagnosis of depression (ICD-10 code F32 or F33) in the previous 90 days. In the group of individuals aged 18–24 years, we will also consider testing the model performance separately for individuals initiating their SSRI in primary and specialist care settings.

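### All models are tuned on AUC alone and their probabilities averaged with no recalibration step stated, yet the result is read as absolute risk at fixed cut-offs; the 2% and 5% cut-offs are also paired with the wrong metric

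*Protocol article*

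**What the plan says.** **Tuning.** Under Model development, Broad predictor model, the grid search with 10-fold stratified cross-validation has a single criterion: "we will choose the set of hyperparameters that maximise the AUC for each model". The Restricted predictor model section repeats it: "We will use the AUC as the evaluation criterion for hyperparameter tuning".

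**Combination.** Directly after tuning, "The class probabilities of each model will be summed and averaged", and "In effect, the predictions of each model will be weighted equally". The restricted stage follows suit: "We will also produce an ensemble prediction in the same way as described for the broad predictor model". The broad-model section adds that "the final prediction will consist of the class with the highest average probability". With two classes that is a 50% cut-off. The AUC, the calibration plot and the 1% threshold all need the averaged probability itself, so I take that to be the quantity meant.

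**Use.** Model validation and goodness of fit plans sensitivity, specificity and both predictive values at a predicted risk of 1%, chosen because it is roughly the outcome prevalence. A person above it is taken to be above population risk. The section then says: "We will also report calibration performance at a 2% and 5% risk cut-off".

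**Calibration.** The Abstract wants a model with "high predictive performance in terms of discrimination and calibration". A Brier score and calibration plot are planned for the broad model and the selected restricted model. In selecting the restricted model, calibration is named once, without a metric, in the sentence on falling back to the elastic net. The next sentence selects on a statistically significant AUC advantage alone.

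**The concern.** AUC depends only on how predictions rank people. Predictions that are too extreme, too shrunken or shifted can have the same AUC as correct ones. Along a penalty path the ranking does change, but often so little that AUC is nearly flat while the spread of predicted risks changes a great deal. A criterion that is flat over that range can settle anywhere on it.

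The 1% rule is valid only if a stated 1% means about 1%. The four model types also need not share a scale: a support vector machine's native score is not a probability, and boosted trees and neural nets can be over- or under-confident. Equal-weight averaging assumes a common, correct scale.

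At stake are the share of young people labelled high-risk, the reported sensitivity, specificity and predictive values, and the meaning of an individual score in an online tool. The 2%/5% sentence is a separate, smaller matter. Calibration is agreement between predicted and observed risk over the range of predictions, whereas a cut-off is described by its classification results.

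**Working it through.** The article gives no event count, expected AUC or calibration target, so there is no planned figure to reproduce. From the document: prevalence about 1%; cut-offs 1%, 2% and 5%; 10-fold cross-validation; AUC criterion. Everything else below is assumed.

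**Step 1. What AUC cannot see.** Assume true risks logit(p) = a + 1.1·Z, with Z standard normal and a = −5.178, so that mean risk is 1%. A simulation of 1,000,000 people gives AUC 0.7753. Doubling every predicted odds leaves AUC at 0.7753, but raises the share above 1% from 29.8% to 54.1%.

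**Step 2. Effect of a given calibration slope c.** Let the reported logit be b + logit(p)/c, with b set to keep the mean at 1%. AUC is again unchanged. The share above cut-off t is

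1 − Φ{[c·(logit t − b) − a] / 1.1}.

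Example: c = 1.4, b = −1.197, t = 5%. Logit t = −2.944; −2.944 + 1.197 = −1.747; × 1.4 = −2.446; + 5.178 = 2.732; / 1.1 = 2.48; upper tail about 0.65%.

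| Calibration slope | above 1% | above 2% | above 5% | sensitivity at 5% |
|---|---|---|---|---|
| 0.8 (too extreme) | 25.7% | 12.2% | 3.2% | 0.21 |
| 1.0 | 29.8% | 12.1% | 2.1% | 0.16 |
| 1.4 (too shrunken) | 35.1% | 10.1% | 0.65% | 0.075 |
| 2.0 | 39.4% | 6.1% | 0.05% | 0.01 |

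In relative terms the damage is greatest in the upper tail. Between slopes 0.8 and 1.4 the share above 5% varies about five-fold (3.2/0.65). At 2% the change is modest unless shrinkage is marked.

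**Step 3. Which slopes does AUC tuning produce?** Ridge logistic regression with about 1% prevalence and the penalty chosen by 10-fold cross-validated AUC, in three sets of simulated data. The first two sets had 60 binary predictors and 60,000 people.

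| Set | slope, AUC-tuned | slope, log-loss-tuned |
|---|---|---|
| 3 datasets | 0.86, 1.09, 26.9 | not reported |
| 6 datasets | 0.93, 1.08, 1.18, 1.19, 1.22, 1.29 | 0.89 to 1.06 |
| 3 datasets | 0.81 to 1.41 | 0.96 to 1.17 |

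Eleven of the twelve AUC-tuned slopes lie between 0.81 and 1.41. In the twelfth, AUC chose the heaviest penalty tried: nobody exceeded 2%, against 2.1% of people at a near-calibrated penalty (slope 0.94), with test AUC 0.602 against 0.603. In each dataset of that first set, test AUC varied by less than 0.01 over penalties whose slopes ran from about 0.8 to 27 or more.

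**Step 4. At the planned 1% cut-off.** In the six-dataset set, AUC tuning flagged 34–39% and log-loss tuning 32–37%, with the same mean predicted risk. In the last set the flagged share moved by 1 to 2 points.

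**Step 5. The 2%/5% sentence.** It stands after a list of classification metrics given for 1% only. Read literally, it asks for a property of the whole risk range at a single point, and leaves the classification results at 2% and 5% unplanned.

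**The case against.** **Calibration is not ignored.** A plot and Brier score are planned, calibration is mentioned in model selection, the text notes that the elastic net intercept can be changed for another population, and continuous scores are said to be possibly more useful than cut-offs. This stands: miscalibration would be visible. But no action is tied to seeing it, and changing the intercept is offered for transport to other populations, not as a step in this analysis.

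**AUC tuning is a common and cited choice.** This also stands. The tuning criterion is not itself an error, and most simulated runs gave tolerable slopes.

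**The article is condensed.** A reader might infer that uncalibrated scores are averaged and that nearly everyone would then exceed 1%. The document does not support that. It averages class probabilities, which for a support vector machine already implies some mapping from score to probability, and it does not say that recalibration is excluded. An outcome that drastic would need a base model trained with class weighting or resampling, and neither is mentioned: the stratification concerns only the folds, and the training and testing samples are defined by date without random sampling. The supportable statement is that no recalibration step is stated.

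**The 2%/5% wording might mean observed against predicted risk among people above each cut-off.** That is possible, but the text does not say so, and classification results there would still be unplanned.

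**Conclusion.** The point holds in a limited form. The tuning criterion and the combination rule are fixed, neither looks at calibration, and both feed a rule that reads predictions as absolute risk. That is a gap between the plan's stated goal and its procedure, not evidence that the models will be miscalibrated.

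The likely size is modest at 1%: a few percentage points in the share flagged. It is larger in relative terms at the higher cut-offs, most clearly at 5%, and extreme over-shrinkage is an occasional possibility (one run in twelve). These figures rest on assumed data and on ridge regression only. Elastic net, boosted trees, neural nets and support vector machines were not simulated, so the range is an illustration, not a forecast.

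The 2%/5% sentence names the wrong quantity whatever the simulations show.

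**What to change.** 1. Keep AUC tuning if preferred; log loss is an option, not a requirement. Recalibrate each base model before averaging by fitting a logistic intercept and slope to its out-of-fold predictions in the training sample.
2. Recalibrate the selected restricted model in the same way before applying any cut-off.
3. In the testing sample, report calibration intercept and slope alongside the plot. Recalibration within 2007–2017 data cannot correct drift into 2018–2020, and these two numbers would show it.
4. Replace the 2%/5% sentence with a plan to report sensitivity, specificity, PPV and NPV at 2% and 5%, as at 1%.

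The cost is a few lines of code on predictions that the cross-validation already produces. An intercept-and-slope correction with a positive slope keeps each model's ranking, so each base model's AUC is unchanged. The ensemble's AUC may shift slightly because the averaged scales change.

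### The ensemble's final prediction is defined as a class label, an implicit 50% cut-off, although the planned evaluation needs a continuous risk at about 1% prevalence

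*Protocol article*

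**What the plan says.** In the Broad predictor model part of Model development, the ensemble is built in two steps. First, "The class probabilities of each model will be summed and averaged". Then "the final prediction will consist of the class with the highest average probability", and a parenthesis identifies this as the ensemble prediction. The Restricted predictor model part repeats the construction: "We will also produce an ensemble prediction in the same way as described for the broad predictor model". The ensemble is then one of the candidates in the DeLong comparison of AUCs that decides the final model.

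Model validation and goodness of fit sets out the evaluation. "Overall classification performance using area under the receiver operating characteristic curves (AUC) will be estimated for all models". The broad model and the selected restricted model also get a concordance index, a Brier score, a calibration plot and "sensitivity, specificity, positive and negative predictive values at the risk threshold of 1" per cent. That threshold was chosen "given that this is the approximate prevalence of suicidal behaviour within 30 days after SSRI initiation in Swedish registers". The protocol adds: "We will also report calibration performance at a 2% and 5% risk cut-off".

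**The concern.** The two sections describe different outputs. With two classes, choosing the one with the higher average probability means predicting an event only when the averaged risk exceeds 50%. The evaluation section treats anyone above 1% as high-risk, a threshold fifty times lower, and uses measures that need a graded risk.

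Two results are at stake. One is the reported performance of the broad-predictor ensemble, which is the model that aim A sets out to explore. The other is the choice of the restricted model, because a candidate must have a significantly better AUC than the others, the ensemble included. If the ensemble enters as a 0/1 label, that comparison reflects how the output was coded, not how well averaging predicts.

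**Working it through.** The protocol gives no event count, sample size or expected AUC, so there is no figure of its own to reproduce. The check asks what the class rule yields at the stated prevalence.

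**Inputs from the protocol.** Prevalence of about 1%; four equally weighted class probabilities; the class rule; evaluation at 1%, 2% and 5%. No class weighting or resampling is described.

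**Assumptions.** Predicted risks average to the prevalence (step 1). Risks are calibrated and logit-normal, with AUC 0.70 to 0.90 (steps 2 and 4). Prevalence is varied from 0.5% to 2% as a sensitivity range.

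**Step 1: bound without a distribution.** For a non-negative risk R, Markov's inequality gives P(R ≥ 0.5) ≤ E(R)/0.5. At 1% prevalence this is 0.01/0.5 = 2%. At 0.5% it is 1%, and at 2% it is 4%. This limits the share labelled as events but not the AUC of the label.

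**Step 2: assumed risk distribution.** Let logit(R) = a + s·Z, with Z standard normal. Solve for a to give 1% prevalence and for s to give the target AUC. A binary label has AUC = (sensitivity + specificity)/2.

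| AUC of risk | s | Share above 50% | Sensitivity | Specificity | AUC of label | Brier, label | Brier, risk |
|---|---|---|---|---|---|---|---|
| 0.70 | 0.74 | 0.0000% | 0.0000 | 1.00000 | 0.5000 | 0.01000 | 0.00983 |
| 0.75 | 0.96 | 0.0000% | 0.0000 | 1.00000 | 0.5000 | 0.01000 | 0.00976 |
| 0.80 | 1.21 | 0.0006% | 0.0003 | 1.00000 | 0.5002 | 0.01000 | 0.00964 |
| 0.85 | 1.50 | 0.0082% | 0.0048 | 0.99997 | 0.5024 | 0.00999 | 0.00940 |
| 0.90 | 1.90 | 0.0509% | 0.0313 | 0.99980 | 0.5156 | 0.00988 | 0.00893 |

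For the last row, (0.0313 + 0.99980)/2 = 0.516. The label's Brier score is essentially the prevalence. Across prevalences of 0.5% to 2%, the share above 50% runs from 0 to 0.24% and the label's AUC from 0.500 to 0.537.

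**Step 3: the cut-offs.** A 0/1 label cut at 1%, 2% or 5% gives the same split each time, namely the 50% split. It also gives no calibration curve, because it takes only the values 0 and 1.

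**Step 4: the same model, using the averaged probability.** At 1% prevalence and a 1% cut:

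| AUC | Share flagged | Sensitivity | Specificity | PPV |
|---|---|---|---|---|
| 0.70 | 36% | 0.65 | 0.64 | 1.8% |
| 0.80 | 28% | 0.73 | 0.72 | 2.6% |
| 0.90 | 19% | 0.82 | 0.81 | 4.3% |

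Over this AUC range, sensitivity is 65% to 82% from the averaged risk and 0% to 3.1% from the class label.

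**Step 5: model selection.** With an AUC near 0.5, the ensemble could hardly be the significantly better model. Any reasonably discriminating base model would beat it easily, so the requirement to outperform the ensemble would test almost nothing.

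**The case against.** The strongest reply is that the continuous quantity is already there. The averaged probability is formed immediately before the class rule, and every planned measure follows from it. The evaluation section also points to that use. It classifies "any child, adolescent or young adult with a predicted risk greater than 1" per cent as high-risk, plans a calibration plot and remarks that continuous scores may be more flexible than cut-offs. An analyst working from both sections would probably evaluate the average and treat the class rule as a stock description of soft voting. This stands as evidence of likely intent, and it makes the repair easy. It does not remove the conflict, because no section names the averaged probability as the ensemble output and the restricted stage imports the definition as written.

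A second reply is that the harm in model selection is limited: a degenerate ensemble can neither win nor block another model, and elastic net is the default. That is true, but an ensemble that cannot block is no longer the comparator that the rule calls for.

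A reader might also infer four stronger things, which the protocol does not support:

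- **That the planned measures cannot be obtained at all.** They can, from the average. AUC and Brier score can even be computed from labels, though they are then uninformative.
- **That predictor selection is damaged.** The top 30 predictors come from each base model, not from the ensemble.
- **That only a handful of people would be labelled as events.** A head count needs a test-set size, which the protocol does not give, and an assumed AUC.
- **That each base model must be recalibrated before averaging because tuning uses AUC and a support vector machine gives no natural probability.** The protocol already says that class probabilities are averaged. Tuning on AUC does not show that they lack a probability scale, and calibration of the broad model is to be checked. Recalibration is a reasonable option, not the correction of an error.

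**Conclusion.** The point holds as a contradiction in a stated rule. Followed literally, the ensemble output is a near-constant label that cannot usefully support the protocol's own evaluation or act as a fair candidate in the restricted-model comparison.

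The 2% ceiling on the share labelled as events needs only that predicted risks average to the 1% prevalence. The smaller shares, and the label AUC near 0.5, rest on the assumed calibrated logit-normal model with AUC 0.70 to 0.90. Class weighting or resampling would put more people above 50%, but uncorrected averages would then not be risks to set against a 1% threshold. The extent of harm depends on whether analysts follow the wording or the apparent intent, so the rule should be corrected before the models are evaluated.

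**What to change.** Delete the class rule and state in both the broad and restricted stages:

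*The ensemble prediction is the mean of the four models' predicted probabilities; this continuous risk is used for AUC, DeLong comparisons, Brier score, calibration and the 1%, 2% and 5% cut-offs.*

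The cost is one sentence, with a cross-reference in the restricted stage. The averages are already produced, so no further data, fitting or tuning is needed. Recalibrating base models before averaging can be left to the authors' judgement.

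### Permutation importance is computed in the training data with no held-out folds required, so a base model that still overfits after tuning can put noise predictors in its top 30

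*Protocol article*

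**What the plan says.** Under Predictors, Restricted predictor model, the protocol article states the goal: "We will identify the top 30 predictors that contributed most to predictive performance in each of the base models in stage A". Under Model development, Broad predictor model, importance is again explained as contribution to predictive performance, and the top 30 predictors "in each of the base models (when applied in the training data) will be extracted using permutation-based feature importance".

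The training sample is formed "using all data from 1 January 2007 to 31 December 2017" and the testing sample "using all data from 1 January 2018 to 31 December 2020". Cross-validation appears only as a tuning device: "we will identify hyperparameters by a grid search with 10-fold stratified cross-validation", with the settings chosen to maximise AUC. Nowhere is it said that the permutation is done on held-out folds.

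If permutation is not computationally feasible, the ranking falls back on the "predictor importance score from the XG model and absolute beta coefficients from the EN model". The scale of those coefficients is not stated.

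The four lists are pooled, screened by clinical input and the evidence base, and published with reasons. Age, sex and previous suicide attempt enter regardless of rank.

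**The concern.** The stated target is contribution to predictive performance, which is a property of new patients. Permuting a predictor in the records used for fitting measures how much the fitted model relies on that predictor, and this includes reliance on chance patterns. The two agree when training and new-data performance are close, and can part when they are not.

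At stake is the quality of the list that goes to clinical review. A base model that fits its training data much more closely than new data can give places in its top 30 to predictors with no real effect and leave out some that have one. The pooled list will be published, so readers would also see such predictors presented as important.

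The fallback has a related, smaller problem. A raw absolute coefficient ignores how common the predictor is, so a rare binary diagnosis can rank high while adding almost nothing to discrimination.

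**Working it through.** The plan gives no figure to reproduce, so the check is a predictor count, a set of illustrative simulations and a short calculation for the fallback.

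**1. Size of the filter (Tables 1–3).** Table 2 has 23 diagnosis groups and Table 3 has 8 drug groups. Candidates: 23 × 2 time windows + 8 × 2 time windows + 23 parental + 6 others (sex, native born, age, prescriber practice, parental education, parental suicide) = 46 + 16 + 23 + 6 = 91. Each list keeps 30/91 = 33%. Four lists give 4 × 30 = 120 places, more than the number of candidates.

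**2. Does training-data importance reward noise?** Boosted trees were simulated with 91 independent binary predictors, 25 of them with a true effect (log odds ratio 0.2–1.0). The event rate was about 1%, in line with the prevalence given under Model validation and goodness of fit. Mean AUC drop for pure-noise predictors:
- fitting data, mildly regularised model: 0.0002–0.0004
- fitting data, overfitted model: 0.0015–0.0031
- fresh data: −0.0002 to 0.0001

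So the mechanism is real, and it grows with overfitting.

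**3. Does it change the top 30?** Mean number of true predictors in the top 30:

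| Base model | Training AUC / new-data or CV AUC | True effects | Training ranking | Held-out or fresh ranking |
|---|---|---|---|---|
| Boosted trees, depth 2, N = 20,000, 5 runs | 0.82 / 0.74 | 25 | 18.0 | 17.8 |
| Boosted trees, depth 2, N = 60,000, 5 runs | 0.78 / 0.74 | 25 | 21.2 | 21.4 |
| XGBoost tuned by CV, N = 60,000, 8 runs | not recorded | 15 | 12.9 | 12.3 |
| XGBoost tuned by CV, N = 30,000, 7 runs (90 predictors) | 0.77–0.84 / 0.70–0.77 | 25 | 18.0 | 17.0 |
| Boosted trees, depth 6, untuned, N = 20,000, 5 runs | 0.99 / 0.64 | 25 | 12.2 | 14.6 |
| Small neural net, tuned, 3 runs | not recorded | 25 | 18.3 | 17.7 |
| RBF SVM tuned by CV, N = 4,000, 4 runs | 0.95–0.97 / 0.57–0.66 | 25 | 10.25 | 15.25 |

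The last two rows are means of single runs. Neural net: 20, 19, 16 against 20, 17, 16. SVM: 9, 12, 10, 10 (sum 41) against 13, 17, 12, 19 (sum 61). The SVM difference is (61 − 41)/4 = 5 places of 30.

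Where training and held-out AUC are reasonably close, the two rankings recover about the same number of true predictors. Where a wide gap remains, as in the tuned SVM, the training ranking loses.

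**4. Fallback.** For one binary predictor with prevalence p0 in non-cases and p1 in cases, the AUC gain over 0.5 is (p1 − p0)/2. The values below are assumed.
- Rare: p0 = 0.001, odds ratio 3. β = ln 3 = 1.10. Odds in cases = 3 × 0.001001 = 0.003003, so p1 = 0.00299 and the gain = 0.001.
- Common: p0 = 0.20, odds ratio 1.8. β = ln 1.8 = 0.59. Odds in cases = 1.8 × 0.25 = 0.45, so p1 = 0.310 and the gain = 0.055.

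Raw |β| puts the rare predictor first. With SD = √(p0(1 − p0)), |β| × SD is 1.10 × 0.0316 = 0.035 against 0.59 × 0.40 = 0.24, which restores the order.

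In 12 simulated cohorts with ridge regression fitted on standardised predictors, choosing the top 30 by back-transformed |β| gave a test AUC of 0.660, against 0.684 by |β| × SD. With a tuned penalty on unstandardised predictors the gap vanished (0.685 against 0.683). In 6 further cohorts the change altered the elastic net list but gave the pooled XGBoost and elastic net list no consistent AUC gain.

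**The case against.** The strongest reply is that the plan already controls overfitting before it ranks anything. Hyperparameters are chosen by held-out AUC, and in the eight tuned XGBoost runs this picked depth 1 seven times and depth 2 once. For XGBoost, and for the small neural net, that reply stands. It does not cover the SVM, which kept a large gap between training and cross-validated AUC after tuning.

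Second, a true predictor drops out of the pool only if all four models omit it, and noise that gets in must still pass clinical review. This limits the harm. Pooling does not keep noise out, though, since one list is enough to admit a predictor.

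Third, importance computed on held-out folds inside 2007–2017 would still be importance in the training data, so the wording may be compatible with the remedy. That is possible, but the text neither says so nor excludes it, and the natural reading is the fitted records.

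Fourth, age on a 1-year scale would have a small raw coefficient, but this has no consequence because age is included regardless.

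A reader might infer more: that the shortlist will be made of overfitted predictors in place of ones that work in new patients, or that the restricted model will perform worse. The documents do not support either. Tuning, pooling and clinical selection stand between the ranking and the model, and no restricted-model performance was computed from training-based and held-out permutation lists.

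**Conclusion.** The point holds as a specification weakness with limited consequences. The plan defines importance as contribution to predictive performance, but measures it where fitted noise also counts. The effect on a single list ranges from nil (tuned XGBoost, small neural net) to about 5 of 30 places (tuned RBF SVM).

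The outcome is a possibly less efficient shortlist. The reported 2018–2020 AUC is not made optimistic by this step, because that sample plays no part in the ranking; keeping it out is correct.

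The sizes rest on assumptions that the article does not give: cohort size, effect sizes, predictor prevalences, mainly additive and independent effects, and small tuning grids. The SVM result comes from four runs at N = 4,000, and it need not carry over to the real cohort or to another kernel. Additive data favour shallow trees, so strong interactions could bring back some difference for XGBoost. The fallback point is secondary: its effect depends on a coefficient scale that the article does not state, and no consistent gain was seen in the pooled list.

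**What to change.** State in Model development, Broad predictor model, that permutation importance is computed within the 2007–2017 training sample on the held-out folds of the 10-fold cross-validation, with each model fitted without that fold, and averaged over the ten folds. Leave the 2018–2020 sample untouched.

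If the fallback is used, state that elastic net coefficients are ranked on the standardised scale (|β| × SD of the predictor).

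The cost is modest extra coding and computing time. Each record is held out once, so the number of permuted predictions stays the same, and the ten fits per model at the chosen settings can be kept from tuning or rerun. No new data are needed.
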